## Abstract

**Graphical abstract:**

[figure not shown]

**Abstract:**

Threatened miscarriage is a common complication of early pregnancy characterized by symptoms of vaginal bleeding with/without abdominal cramps/pain in the first trimester. Progestogens are often administered for the management of this condition. Presented herein is the protocol of an ongoing, multicentric clinical trial to investigate the efficacy and safety of micronized progesterone (natural progestogen) compared to dydrogesterone (synthetic isomer of progesterone). A total of 304 eligible pregnant women aged 20–39 years, diagnosed with threatened miscarriage, will be enrolled during 5–12 weeks of gestation and randomized equally to receive either oral dydrogesterone (40 mg stat, followed by 10 mg three times a day) or oral micronized progesterone (200 mg two times a day) up to one week after stoppage of bleeding or if bleeding does not stop, then treatment will be continued till a maximum of 14 weeks of gestation (unless miscarriage is confirmed earlier or the investigator decides to prolong treatment for better outcome or if bleeding relapses). Scheduled visits after enrollment will be conducted during 6–13, 8–14, 18–20 and 24–26 weeks of gestation, in addition to a visit at the end of treatment at 14 weeks and another after parturition. The primary endpoint of the study is the miscarriage rate before 20 weeks of gestation. Secondary endpoints include the ongoing pregnancy rate at 24 weeks, treatment-induced changes in serum levels of cytokines and time to symptom resolution. Apart from the incidence of treatment-emergent adverse events, safety endpoints include changes in complete blood count and the results of liver and kidney function tests from baseline to 14 and 24–26 weeks of gestation. Delivery outcomes are exploratory endpoints of the study.

**Lay summary:**

Almost one out of four women face miscarriage during the first trimester of pregnancy; initial symptoms include vaginal bleeding with/without abdominal cramps/pain. This paper presents the plan of how an ongoing, multicentric study will be conducted to compare the efficacy and safety of oral medications known to reduce chances of miscarriage: micronized progesterone (which is a natural female sex hormone) versus synthetic progesterone. Women aged 20–39 years who are at risk of miscarriage during the first trimester of pregnancy will be randomly treated with either medication till one week after stoppage of bleeding during early pregnancy. If bleeding does not stop, treatment will be continued till a maximum of 14 weeks of pregnancy (unless miscarriage is confirmed earlier). The participants will be monitored until delivery. The study will evaluate the proportion of participants who experience miscarriage before 20 weeks of pregnancy and those who have an ongoing pregnancy at 24 weeks. It will also look at the time taken for relief from symptoms such as vaginal bleeding and abdominal pain, outcomes of delivery and incidence of any untoward event. In addition to routine tests and scans, additional tests will check for levels of biochemical parameters in the body, which are regulated by the natural or synthetic progesterone.

**Clinical trial registration number:**

CTRI/2024/02/063174 [Registered on: 26/02/2024].

## Introduction

Threatened miscarriage, a common complication of early pregnancy, is defined as ‘bleeding before 20 weeks of gestation in the presence of an embryo with cardiac activity and a closed cervix’. Vaginal bleeding is often accompanied by abdominal cramps/pain. Nearly ∼25% of women experience threatened miscarriage with the rate of early pregnancy loss being ∼11% after a live fetus is detected on ultrasonography (USG) (Hendriks *et al.* 2019). Threatened miscarriage may be associated with complications later in pregnancy. Bed rest is recommended for preventing miscarriage, but there is a dearth of convincing evidence supporting its effectiveness (Qureshi 2009). Insufficiency of progesterone during the luteal phase of menstrual cycle and early pregnancy is one of the hypothesized causes of miscarriage. Therefore, luteal support is used as a management strategy (Verma & Yadav 2021) and is achieved by the administration of progestogens (such as progesterone and dydrogesterone) or human chorionic gonadotrophin (hCG) (Qureshi 2009). Results from different clinical trials and meta-analyses have shown that progestogens may be beneficial to women with previous miscarriages and that their effects in women with no previous miscarriages remain uncertain (Coomarasamy *et al.* 2020, Devall *et al.* 2021, Zhao *et al.* 2024).

Progesterone, produced by the corpus luteum and later by the placenta, plays essential endocrinologic functions in the maintenance of pregnancy (Verma & Yadav 2021). It stimulates the growth of blood vessels supplying the endometrium, stimulates the endometrium to secrete nutrients to nurture the newly formed embryo, prepares the uterine lining for implantation and sustains the endometrium throughout pregnancy. It also inhibits inflammatory reactions by downregulating cytokine production and immune cell activation (Raghupathy & Szekeres-Bartho 2022). When used for treatment, progesterone is usually administered in a micronized form as it has very poor pharmacokinetics when taken orally (Verma & Yadav 2021). The STOP (McLindon *et al.* 2023) and PRISM (Coomarasamy *et al.* 2019) trials did not observe a significant advantage of vaginal micronized progesterone in improving live birth rate over placebo.

Dydrogesterone (6-dehydro-9β, 10α-progesterone) is similar in molecular structure and pharmacological effects to endogenous progesterone, but is more potent and has higher absorption and bioavailability than the natural progesterone due to a comparatively higher affinity for the progesterone receptor. Some studies have also highlighted the therapeutically beneficial immunomodulatory functions of the molecule (Hudić *et al.* 2011, Ibrahim *et al.* 2020). Dydrogesterone significantly decreases the levels of Th1 (proinflammatory) cytokines (such as interferon (IFN)-γ and tumor necrosis factor (TNF)-α) while significantly elevating the levels of Th2 (anti-inflammatory) cytokines (such as interleukin (IL)-4, IL-6 and IL-10). The overall effect is a significant reduction in the Th1/Th2 ratio, indicating a shift in the maternal cytokine balance from proinflammatory toward anti-inflammatory bias. This ability of dydrogesterone to downregulate proinflammatory cytokines is conducive to the continuation of a healthy pregnancy as these could otherwise be detrimental during gestation (Raghupathy & Szekeres-Bartho 2022). A significant advantage of dydrogesterone is that it retains its immunomodulatory activity even after it is converted to its major metabolite when consumed orally. In addition, it does not inhibit ovulation at recommended doses, has not been reported to cause metabolic side effects, and is devoid of estrogenic or androgenic properties (Ibrahim *et al.* 2020, Raghupathy & Szekeres-Bartho 2022), and there is no convincing evidence of any causal association with fetal abnormalities; these attributes attest to the safety of the molecule (Katalinic *et al.* 2022). With respect to its use in threatened miscarriage, no significant difference has been reported compared to placebo in continuing pregnancy (Kuptarak & Phupong 2024). Use of oral dydrogesterone was preferred over vaginal progesterone in patients with vaginal bleeding during early pregnancy and a history of recurrent early pregnancy loss based on a numerically higher number of patients in the oral dydrogesterone group having successful continuation of pregnancy compared to the progesterone group (Kale *et al.* 2021).

The available evidence prompted us to investigate the efficacy of oral dydrogesterone versus oral micronized progesterone. As Devall *et al.* mentioned, there exists uncertainty over the effectiveness and safety of alternative progestogen treatments in threatened miscarriage (Devall *et al.* 2021). A pilot study pointed toward comparatively better symptom relief in patients treated for two weeks with oral dydrogesterone, although miscarriage rates were comparable between patients treated with oral dydrogesterone versus those treated with oral micronized progesterone (Siew *et al.* 2018), a finding that was corroborated by a study in which patients were treated till 12 weeks of gestation (Lou *et al.* 2021). The latter study also reported that the levels of sex hormones were significantly elevated and the incidence of adverse events (AEs) was significantly reduced in the dydrogesterone arm (Lou *et al.* 2021). Along similar lines, a comparatively better safety profile was reported in patients treated for two weeks with oral dydrogesterone compared to those treated with oral micronized progesterone (Shaikh *et al.* 2022). In a more recent study, resolution of pain and vaginal bleeding was better in patients treated till 12 weeks of gestation with oral dydrogesterone compared to those treated for similar duration with oral micronized progesterone (Verma & Yadav 2021). However, these studies comparing oral dydrogesterone versus oral micronized progesterone were single-center trials, in which patients were treated either for a predetermined period of two weeks or till 12 weeks of gestation.

The current study aims to combine the knowledge gained from the above studies and overcome some of their limitations. Accordingly, a multicentric, prospective clinical trial has been designed to compare oral dydrogesterone versus oral micronized progesterone in threatened miscarriage, wherein patients will be treated not for any predefined duration but till one week after stoppage of bleeding or if bleeding does not stop, then treatment will be continued till a maximum of 14 weeks of gestation (unless miscarriage is confirmed within 14 weeks of gestation or the investigator decides to prolong treatment for better outcome or if bleeding relapses). In addition to investigating miscarriage rates, symptom resolution, delivery outcomes and treatment-emergent AEs (TEAEs), this study aims to compare the immunomodulatory roles of the molecules being investigated by the assessment of cytokine levels as this aspect has not been explored in any of the aforementioned studies (Siew *et al.* 2018, Lou *et al.* 2021, Verma & Yadav 2021, Shaikh *et al.* 2022).

## Objectives

The primary objective of the study is to compare reduction in miscarriage rate before 20 weeks of gestation between the two treatment arms. The secondary objectives are to compare the following between the two treatment arms: rate of ongoing pregnancy at 24 weeks, rate of live births, safety of the study medications based on TEAEs, levels of immunomodulation markers and time to symptom resolution (Table 1).

**Table 1 tbl1:** Study objectives.

**Primary objective**
• To compare the reduction in miscarriage rate before 20 weeks of gestation between pregnant women with threatened miscarriage treated with oral dydrogesterone versus oral micronized progesterone
**Secondary objectives**
• To compare the rates of ongoing pregnancy at 24 weeks and live births between women with threatened miscarriage treated with oral dydrogesterone versus oral micronized progesterone • To compare the safety of oral dydrogesterone versus oral micronized progesterone based on TEAEs in pregnant women with threatened miscarriage when treated with either • To compare the levels of immunomodulation markers, i.e., serum levels of cytokines (IL-4, IL-10, IFN-γ and TNF-α) in pregnant women with threatened miscarriage, before and after treatment with oral dydrogesterone versus oral micronized progesterone • To compare the time to symptom (vaginal bleeding and/or abdominal pain) resolution between women with threatened miscarriage treated with oral dydrogesterone versus oral micronized progesterone

TEAEs, treatment-emergent adverse events; IL, interleukin; IFN, interferon; TNF, tumor necrosis factor.

### Ethical considerations

The study is being conducted in accordance with the principles of Declaration of Helsinki, Good Clinical Practice (GCP) guidelines as per the International Council for Harmonization (ICH) of technical requirements for pharmaceuticals for human use, GCP guidelines issued by the Central Drugs Standard Control Organization (CDSCO), guidelines for clinical trials on pharmaceutical products in India as mentioned in New Drugs and Clinical Trials (NDCT) rules 2019 and guidelines set for clinical research by the Indian Council for Medical Research (ICMR), 2006, and Drugs and Cosmetic Rules, 1945. Patient recruitment was initiated only after obtaining written approval on the protocol from the ethics committee of each study site. Written informed consent will be obtained from every participant or her legally authorized representative before enrollment. Participants will be identified throughout and after study completion by allotted unique numbers; confidentiality will be maintained at all times.

### Trial registration

This trial has been registered with the Clinical Trials Registry-India (CTRI) on February 26, 2024 (reference number: CTRI/2024/02/063174).

### Study design and settings

This ongoing investigator-initiated study is a prospective, multicenter, open-label, randomized controlled interventional trial that will be conducted in 20- to 39-year-old pregnant women diagnosed with threatened miscarriage in their first trimester. The study is currently at the stage of patient screening and enrollment from multiple sites across India in order to ensure representation of investigators and patients from diverse populations. The study sites are as follows: Paras Hospitals (Gurugram, Haryana), IPGME&R and SSKM Hospital (Kolkata, West Bengal), Ramakrishna Medical Centre (Tiruchirappalli, Tamil Nadu), Dayanand Medical College & Hospital (Ludhiana, Punjab), Nowrosjee Wadia Maternity Hospital (Mumbai, Maharashtra), Manipal Hospital (Bengaluru, Karnataka), Sum Ultimate Medicare Hospital (Bhubaneswar, Odisha), Udyan Health Care Pvt. Ltd (Lucknow, Uttar Pradesh) and B. J. Medical College & Civil Hospital (Ahmedabad, Gujarat).

### Study endpoints

The study protocol outlines primary and secondary endpoints along with safety and exploratory endpoints, as mentioned in Table 2.

**Table 2 tbl2:** Study endpoints.

**Primary endpoint**
• Miscarriage rate before 20 weeks of gestation
**Secondary endpoints**
• Ongoing pregnancy rate at 24 weeks • Change in serum levels of cytokines (IL-4, IL-10, IFN-γ and TNF-α) from baseline to the end of treatment • Time to symptom (vaginal bleeding and/or abdominal pain) resolution
**Safety endpoints**
• TEAEs • Changes in CBC • Change in results of LFTs from baseline to 14 and 24–26 weeks of gestation • Change in results of KFTs from baseline to 14 and 24–26 weeks of gestation
**Exploratory endpoints**
• Rate of live birth • Mode of delivery • Gestational age and birth weight of newborn • Resuscitation requirements • Congenital anomalies in the newborn • History of pre-eclampsia

IL, interleukin; IFN, interferon; TNF, tumor necrosis factor; TEAEs, treatment-emergent adverse events; CBC, complete blood count; LFTs, liver function tests; KFTs, kidney function tests.

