### Treatment

Subjects in the test arm will be treated with oral dydrogesterone; the first dose will be 40 mg (stat) and subsequent doses will be 10 mg three times a day. Subjects in the reference arm will be treated with oral micronized progesterone at a dosage of 200 mg two times a day. Except for subjects who face miscarriage within 14 weeks of gestation, rest will be treated up to one week after stoppage of bleeding or if bleeding does not stop, then treatment will be continued till a maximum of 14 weeks of gestation. Continuation of treatment beyond this will solely be at the discretion of the treating physician. If relapse of bleeding is observed after stoppage of treatment, the physician may decide to continue the medication at his/her discretion; relevant details will be recorded.

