### Planned evaluations

Subjects will be screened and enrolled after obtaining written informed consent at Visit 1. Routine pregnancy-specific imaging and laboratory investigations will be done at a central laboratory during study participation. Subjects will be monitored throughout participation for AEs and serious AEs. Activities planned at each study visit are detailed in Fig. 2.

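### The only named anomaly endpoint is restricted to newborns, so anomalies in miscarried, terminated or stillborn pregnancies fall outside it

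*Protocol article*

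**What the plan says.** Table 2 (Study endpoints) lists "Congenital anomalies in the newborn" among the exploratory endpoints, and the Abstract confirms the tier: "Delivery outcomes are exploratory endpoints of the study". The safety endpoints in the same table are TEAEs, blood count, and liver and kidney function tests (for example "Change in results of LFTs from baseline to 14 and 24–26 weeks of gestation"). None of them names a fetal outcome. The safety objective in Table 1 is framed as "based on TEAEs in pregnant women with threatened miscarriage when treated with either".

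On exposure, enrolment is at 5–12 weeks. Under Treatment, if bleeding persists, "then treatment will be continued till a maximum of 14 weeks of gestation", with extension at the physician's discretion. On event reporting, Planned evaluations states "Subjects will be monitored throughout participation for AEs and serious AEs". The Introduction, arguing for the safety of dydrogesterone, gives as one of several attributes that "there is no convincing evidence of any causal association with fetal abnormalities".

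**The concern.** A fetus that is miscarried, terminated after a scan finding, or stillborn does not become a newborn in the sense of this endpoint. Whether a pregnancy reaches that stage is decided after randomization and is close to what the trial measures as its primary outcome. The protocol itself recognizes that malformation and loss are linked: the exclusion criteria in Table 3 include fetal malformation as an established cause of losing an earlier pregnancy.

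If the arms differ in how often affected pregnancies survive, the newborn count can differ with no difference in anomalies, or can hide one. An arm that loses more affected pregnancies would look better on this endpoint, and an arm that sustains more of them would look worse. With a handful of events per arm, one or two cases are enough to change the impression.

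**Working it through.** The article gives no anomaly rate and no figure for this endpoint, so there is nothing of its own to reproduce. The steps below size the restriction.

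**Inputs from the article**
- 152 women per arm and 8% anticipated dropout (Sample size).
- About 11% early pregnancy loss once a live fetus has been seen on ultrasound (Introduction). This is a background figure, used here as an assumption for the trial population.

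**Assumed, not in the article**
- Anomaly prevalence of 2–5% of pregnancies.
- 10–50% of affected pregnancies ending before birth.

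**Step 1: size of the newborn set per arm**
- After dropout: 152 × (1 − 0.08) = 139.8, about 140.
- After loss as well: 139.8 × (1 − 0.11) = 124.5, about 124.
- Leaving the set: 152 − 124.5 = 27.5, about 28. Of these, 12.2 leave by dropout (152 × 0.08) and 15.4 by loss (139.8 × 0.11).
- With loss varied from 5% to 25%, the newborn set is 133 down to 105.

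The 11% concerns early loss. Later terminations and stillbirths would reduce the set further.

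**Step 2: anomalies outside the endpoint, per arm**

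Expected anomalies = 139.8 × prevalence. Uncounted = expected × share ending before birth.

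| Prevalence | Expected | Uncounted at 10% | Uncounted at 50% |
|---|---|---|---|
| 2% | 2.8 | 0.3 | 1.4 |
| 3% | 4.2 | 0.4 | 2.1 |
| 5% | 7.0 | 0.7 | 3.5 |

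**Step 3: how selection could act**

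Take 4.2 anomalies in each arm, so no true difference. If 10% of affected pregnancies end before birth in one arm and 50% in the other, the newborn counts are 4.2 × 0.9 = 3.8 and 4.2 × 0.5 = 2.1. This uses the two ends of the assumed range and shows only the direction and the possible size.

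**Step 4: what is not at stake**

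The smaller set costs little precision. With zero events the one-sided 95% upper bound is 1 − 0.05^(1/n), which is 2.1% for n = 140 and 2.4% for n = 124. The issue is which cases are counted.

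**The case against.** The strongest reply is that these cases need not be lost. TEAEs are a safety endpoint, adverse and serious adverse events are monitored throughout participation, and the Lay summary says participants are followed until delivery. An anomaly found on a scan could be reported by that route. The visit-by-visit list is in Figure 2, which is not shown, and the full protocol may settle how fetal events are classed. This stands as far as it goes. A reader might infer from Table 2 that anomalies in lost pregnancies disappear from the safety data altogether, and the article does not support that. Nor does it say that they are captured: the safety objective concerns TEAEs in the women, and treatment can end a week after bleeding stops, so a finding at the 18–20 week visit may come well after the last dose. Whatever Figure 2 adds, the endpoint's own wording stops at newborns.

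A second reply is that exploratory status is reasonable. That is correct. With about 3 to 7 expected events per arm under the assumed prevalence, no useful test is possible in any tier. A reader might take the tier itself as an error, or read the Introduction's remark on fetal abnormalities as a claim this trial must test. Neither follows: the remark draws on cited literature and is one attribute among several.

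Third, the article states no denominator, so it cannot be said that births are the planned one. This too is right, but it does not remove the problem. With newborns as denominator, the groups compared are selected by survival. With all women as denominator, an affected pregnancy that ends early counts as unaffected.

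Fourth, differential loss would be visible in the miscarriage, ongoing pregnancy and live birth endpoints. That is so for the number of losses, but none of those endpoints shows how many of the lost pregnancies were affected.

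**Conclusion.** The point holds as one of endpoint wording. The only anomaly endpoint the article names is confined to newborns, so it depends on pregnancy survival after randomization and leaves out anomalies in miscarried, terminated or stillborn pregnancies. On the article's own 8% and 11%, the newborn set is about 124 of 152 per arm, with about 15 of the missing 28 removed by loss. How many anomalies go uncounted is not derivable from the article; the 0.3–3.5 per arm rests wholly on the assumed prevalence and share ending before birth.

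The conclusion does not extend to saying that the trial has no record of such anomalies, that the tier is wrong, or that bias in favour of one arm is expected. It is an inexpensive improvement worth making while enrolment continues, and does not put the primary comparison in doubt.

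**What to change.** Reword the endpoint to cover congenital anomalies in any fetus or newborn. Report descriptively by randomized arm:
- the count over all randomized and treated women, including findings from scans, terminations, miscarriages and stillbirths;
- beside it, the number of losses and of dropouts not assessed for anomalies;
- the newborn-only figure as a second line.

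State how anomalies in losses and terminations are ascertained, and whether they are also reported as adverse events. The endpoint may stay exploratory.

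The cost is a change of wording in the endpoint table and a case report form field. Imaging and event monitoring are already planned, so no new examination is needed. The drawback is incomplete ascertainment: most early losses will not be examined closely, and unassessed pregnancies count as unaffected in the all-women rate. That rate is therefore a lower bound, and the shortfall may differ by arm, which is why the unassessed numbers belong beside it.
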